Fibromyalgia (FM) is a chronic syndrome that affects 3.43% of women worldwide, 3.90% in Europe, and 4.2% in Spain [14]. This syndrome has a considerable functional impact on people who suffer from it, as they present chronic pain problems requiring many social, health, and work resources through comprehensive and continuous care [15]. It is estimated that people with FM represent an annual expense of 11,629.03 euros per patient and year in Spain, costing a total of 4223.02 million euros to Spanish health services, which poses a 279.10-euro cost per inhabitant and year [14]. If we consider that, according to the Ministry of Health of Extremadura, a health expenditure of 1549 euros per inhabitant was made in 2016, the expense on fibromyalgia represents 18% of the total health cost per inhabitant in Extremadura. Therefore, any intervention that may help to reduce these percentages could have a positive impact on reducing the costs of the Extremadura health system.

Falls in people with FM amount to 2.5 per year compared to 0.5 for people without FM [16]. Thus, part of the annual health costs of this syndrome comes from falls. The project that we are presenting attempts to reduce costs associated with falls in this population through balance training with the SSE method, conducted by a professional through video-conferencing (Tele-Square Stepping Exercise; Tele-SSE), improving the balance and preventing falls in women with FM. Reviewing the scientific literature, the SSE program appears to improve balance by preventing falls and decreasing the fear of falling in older adults [13], but no publication had studied the benefits of SSE in people with FM.

Therefore, the main objectives of this project are 1) to investigate the applicability, safety, decrease in the number of falls, and incremental cost-effectiveness ratio of a prevention of falls program through Tele-SSE in women with FM, and 2) to identify key factors for its transfer to the public and private social health system, evaluating the acceptability of Tele-SSE in the agents of the social health system in charge of including Tele-SSE in their services offer.

Additionally, this project has a secondary aim to evaluate the effect of Tele-SSE on balance levels, fear of falling, body composition, physical fitness, quality of life related to health and positive health, pain, disability level, depressive symptoms, and cognitive aspects of participants.

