##### Balance

*Time Up and Go Test (TUG).* Participants will carry out three variants of this test based on the covered distances: 2.40 m [28], 3 m [29], and 10 m [30]. This test has been shown to be valid and reliable (ICC = 0.93, SEM = 0.58, MDC = 1.60) [31]. Each participant will start seated on a chair with her arms and trunk supported. The participant will be instructed to stand with the word “go” and walk in a straight line for 2.40 m, 3 m, and 10 m (depending on the test variant), turn 180°, and walk back to the chair to sit on it again. Prior to recording the measurements, a familiarization test will be conducted. After 1-minute rest, the test will be performed twice, separated by the 1-minute rest. Time will be measured from the standing start movement until the participant sits on the chair again, leaning her back on the support of the chair. The best attempts of each variant will be used for analysis. 

*One-leg stance.* Two variants of this test will be performed: Eyes open (ICC = 0.99) and eyes closed (ICC = 0.95). The test consists of timing the time that the person can be in balance on one leg with arms crossed on the upper train. The test begins when the foot is raised from the ground and ends in the following assumptions: 1) When the arms are uncrossed, 2) when the raised foot touches the ground, 3) when the supported foot moves, 4) when more than 45 seconds have elapsed, and 5) when the eyes are opened in the test with closed eyes. The procedure will be repeated 3 times and each time recorded on the data collection sheet [32,33].

*Four square steps test (FSST).* Four squares will be formed by placing adhesive tape on a flat floor. Each square will be numbered. At the beginning of the test, patients who will be standing on square number 1 opposite square number 2 will be asked to walk as fast as possible on each square consecutively (1-2-3-4-4-3-2-1) without touching the gaps and with both feet contacting the floor. The time needed to complete the complete cycle will be taken for analysis. This test has been shown valid and reliable (ICC = 0.98) [34]. 

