##### Tests Familiarization and Reliability

Before each session, there will be a warm-up phase where the participant will have the test procedure explained, including the specific test trial, before it will be carried out.

The different tests inter-session reliability will be evaluated by repeating the tests two weeks after with part of the sample participants. All possible tests will be carried out under single and dual-tasks conditions.

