### 2.8. Statistical Analysis

Baseline characteristics of participants will be presented as the mean (standard deviation) for continuous variables and proportions for categorical variables. The normality will be checked using the Kolmogorov-Smirnov test. Then, two types of analyses will be performed: 1) An intention-to-treat analysis including all participants and 2) a per-protocol analysis using only those participants who complete the study.

**Intention-to-treat analysis.** This analysis will include all randomly assigned participants in their corresponding groups. Multiple imputations will be used to impute lost data. The effects of the intervention on the main and secondary variables will be computed using a repeated measures ANCOVA test, adjusted by age and baseline values. Results shall include the Cohen’s *d* effect size (95% confidence interval) and statistical significance for each dependent variable respect to time and its interaction effects (group × time). Statistical significance shall be established at the conventional level of *p* < 0.05. In sensitivity analyses, the data imputation will be made from the baseline patient data and from those participants who completed the study, in order to avoid estimation biases. 

**Analysis by protocol.** Similar analyses than those described above will be carried out, but only using participants who have attended at least 75% of the sessions.

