## 4. Conclusions

This project will investigate the applicability, safety, decrease in the number of falls, and incremental cost-effectiveness ratio of a 12-month Tele-SSE prevention of falls program in women with fibromyalgia, as well as, the transfer of obtained results to the public and private socio-health economy of Extremadura will be studied. Results of this investigation will help to improve the efficiency and equity of physical therapy services based on tele-exercise in preventing falls in people with fibromyalgia. Furthermore, orientations will be proposed in order to transfer the obtained findings into the social-sanitary system and market. If the interventions proved to be effective and safe, this study would provide feasible and low-cost alternatives for health professionals in the management and treatment of fibromyalgia.

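### Section 2.8 applies an unadjusted p < 0.05 to each of about 48 secondary scores, with no ordering among them, no correction and no statement that they are supportive only

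*Protocol article*

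**What the plan says.** The intention-to-treat paragraph of section 2.8 puts both tiers of outcome under one method: "The effects of the intervention on the main and secondary variables will be computed using a repeated measures ANCOVA test". It then asks for "statistical significance for each dependent variable respect to time and its interaction effects (group × time"), and fixes the threshold: "Statistical significance shall be established at the conventional level of *p* < 0.05". The per-protocol paragraph repeats the exercise: "Similar analyses than those described above will be carried out, but only using participants who have attended at least 75% of the sessions".

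The secondary outcomes are tied to a stated aim in section 1: "this project has a secondary aim to evaluate the effect of Tele-SSE on balance levels, fear of falling, body composition, physical fitness", followed by further domains. Section 2.7.3 gives several scores for most domains. For the Timed Up and Go, for example, "Participants will carry out three variants of this test based on the covered distances". The paragraph on familiarization and reliability adds: "All possible tests will be carried out under single and dual-tasks conditions".

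The document does separate main from secondary measures (Abstract, sections 2.7.1 and 2.7.3). Section 2.8 gives that separation no role in testing. Nowhere is a key secondary score, an order among the secondary scores or a correction stated, and nowhere are the secondary results called supportive or exploratory.

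**The concern.** The 5% level applies to one test. Section 2.8 attaches it separately to every secondary score, so it does not describe the risk of a false claim across the set.

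The overlap between scores makes this more than a formality:
- Balance has eight scores: three Timed Up and Go distances, two one-leg stances, the four-square step test, the Berg scale and the balance confidence scale.
- Fear of falling has two scales, and happiness has two.
- Fibromyalgia impact is measured by both the FIQ and the FIQ-R.
- Three utility-type indices (15-D, SF-6D, HUIv3) sit side by side.

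Followed as written, the rule lets the report state a significant effect on balance, fear of falling or quality of life from whichever variant crosses 0.05. What is at stake is the strength of the secondary claims, not the validity of the analysis of the main measures.

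**Working it through.** **The plan's own figures.** The document states no family-wise error rate and no number of secondary tests, so there is none to reproduce. Its one statistical calculation, the sample size in section 2.3, does reproduce: 2 × (1.96 + 0.84)² × 0.26² / 0.15² = 47.2 per arm, and 47.2 / 0.8 = 58.95, so 59 per arm and 118 in total. It rests on EQ-5D-5L at two-sided 0.05 and does not bear on the secondary scores.

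**Step 1: count the scores.** One total score per test or instrument described in section 2.7.3:

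| Domain | Scores |
|---|---|
| Balance (TUG × 3, one-leg stance × 2, FSST, BBS, ABC) | 8 |
| Fall risk (FRI-21) | 1 |
| Fear of falling (FES-I, VAS) | 2 |
| Body composition (weight, waist, hip, fat, fat-free, lean, bone, muscle index) | 8 |
| Physical condition (6-minute walk, chair stand, arm curl, handgrip, trunk flexors, trunk extensors, back scratch, sit and reach, brisk walk, functional reach, SPPB, IFIS) | 12 |
| Pain (algometer, VAS) | 2 |
| HRQoL (15-D, SF-12 physical and mental, SF-6D, HUIv3) | 5 |
| Sleep | 2 |
| FIQ, FIQ-R | 2 |
| Depression (BDI-II) | 1 |
| Happiness | 2 |
| Physical activity and sedentary behaviour | 3 |
| **Total** | **48** |

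The global impression scale would make it 49. Height, SF-12 dimensions, FIQ-R domains, IFIS items, single algometer points and dual-task versions are left out.

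**Step 2: expected false positives under no effect.** 48 × 0.05 = 2.4 in either direction, whatever the correlation. In favour of Tele-SSE, 48 × 0.025 = 1.2.

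**Step 3: chance of at least one, if independent.** Either direction: 1 − 0.95^48 = 91.5%. In favour: 1 − 0.975^48 = 70.3%.

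**Step 4: allow for correlation.** The document gives no correlations, so a common correlation ρ between test statistics is assumed. Each statistic is written as √ρ·U + √(1−ρ)·E, with U shared. With c = 1.96, the chance of no false positive is the average over U ~ N(0,1) of p(U)^48, where
- either direction: p(U) = Φ((c − √ρ·U)/√(1−ρ)) − Φ((−c − √ρ·U)/√(1−ρ));
- in favour only: p(U) = Φ((c − √ρ·U)/√(1−ρ)).

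One minus that average, by numerical integration:

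| ρ | Either direction | In favour of Tele-SSE |
|---|---|---|
| 0 | 91.5% | 70.3% |
| 0.3 | 79.5% | 43.8% |
| 0.5 | 61.3% | 31.0% |
| 0.7 | 39.9% | 20.0% |
| 0.9 | 19.2% | 9.6% |

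The 50% line is crossed at ρ of about 0.61 for either direction and about 0.22 for a favourable result.

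**Step 5: sensitivity.**
- *Count.* With 40 to 60 scores, the independent figures are 87.1% to 95.4% (either direction) and 63.7% to 78.1% (in favour). At ρ = 0.5 they are 57.1% to 66.4% and 28.9% to 33.8%.
- *Structure.* Grouping 48 scores into 12 domains, with higher correlation within than between domains (200,000 simulated draws), gives 83.4% / 52.2% at within/between 0.5/0.1, 80.3% / 46.5% at 0.5/0.2, 75.8% / 41.1% at 0.5/0.3 and 69.0% / 36.9% at 0.7/0.3 (either direction / in favour).
- *Balance alone.* Eight scores give 33.7% if independent, 25.0% at ρ = 0.5 and 11.9% at ρ = 0.9, in either direction.

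**Limit of the split by direction.** A group × time test over several visits has more than one degree of freedom and no sign. The favourable column treats each score as one signed group comparison and is therefore approximate.

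**The case against.** **The analysis plan may deal with it.** This is a journal article, and the choice of key secondary scores, ordering and multiplicity rules are often left to a fuller document. That limits the severity. It does not remove the point, because section 2.8 is not silent: it states a rule for every variable, and a later plan that labels the secondary scores supportive would have to qualify that published rule.

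**The outcomes are already called secondary, and intervals are required.** Both are true. The document separates four main measures from the rest, so it would be wrong to read the secondary scores as having equal standing with the main ones; the missing hierarchy is within the secondary tier. Section 2.8 also asks for effect sizes with 95% confidence intervals, which is part of the remedy. Neither changes the instruction to declare significance on each score.

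**A stronger reading is tempting.** A reader might infer that a significant secondary benefit is more likely than not even if Tele-SSE does nothing. The figures do not support that. It holds under independence (70%), but the favourable chance falls below 50% once the common correlation passes about 0.22, and the overlap between scores argues against low correlation within domains.

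**Consequences for transfer.** A reader might also infer that chance secondary findings could carry the programme into the health system when falls and cost-effectiveness show nothing. The document does not say so. Section 3 makes the health-system opportunity conditional on showing fall prevention and cost-effectiveness. The closing condition in section 4, "If the interventions proved to be effective and safe, this study would provide feasible and low-cost alternatives for health professionals", does not define effectiveness, but the section opens with the four main measures.

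**Extra tests.** The per-protocol repeat largely duplicates the intention-to-treat tests, and a time effect is not a treatment claim. Neither is counted above.

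**Conclusion.** The point holds: section 2.8 fixes an unadjusted 5% test for each of about 48 overlapping secondary scores without saying that the results are supportive only. Under no effect, about 2.4 scores would be expected to reach p < 0.05, about 1.2 in favour of Tele-SSE. The chance of at least one in either direction ranges from 19% at a common correlation of 0.9 to 92% under independence, roughly 4 to 18 times the stated 5%. For a favourable result the range is about 10% to 70%, against 2.5% for a single test. At least one significant difference in some direction is more likely than not unless the common correlation exceeds about 0.6.

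These figures rest on a count of one total score per instrument, an assumed correlation and one signed comparison per score. The analysis of the main measures is unaffected. What should not be concluded is that a nominally significant secondary score demonstrates an effect.

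**What to change.** In section 2.8:

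- Limit the p < 0.05 significance rule to the main measures.
- State that all secondary measures, including any dual-task versions and the per-protocol repeat, are supportive or exploratory, reported as adjusted group differences with 95% confidence intervals and no claim of significance.
- If claims by domain are wanted, name one score per domain in advance and apply Holm across those scores. With the 12 secondary outcome domains of Table 2 (sociodemographic data aside), the smallest p-value would be compared with 0.05 / 12 = 0.0042. A Bonferroni rule over all 48 scores would require 0.05 / 48 = 0.0010 for each.

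Making a key secondary test depend on a positive primary result is not proposed: there are four main measures and none is designated to act as the gate.

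The cost is two or three sentences, with no new data or participants. The small downside is that nominally significant secondary results can no longer be presented as demonstrated effects.

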### 2.3. Sample Size

The number of participants was calculated based on the change in quality of life assessed using the 5-level Euroqol-5D questionnaire (EQ-5D-5L). As far as we know, there are no available data on the minimum real change in the EQ-5D-5L in fibromyalgia patients, so we have used a reference of pathology that deals with pain, being this real minimum difference of 0.15 [19]. Therefore, a total of 118 participants (Experimental group; *n* = 59 and Control group; *n* = 59) are needed; accepting alpha and beta risks of 0.05 and 0.2, respectively, in a bilateral contrast, to detect a difference equal to or greater than 0.15 units. It is assumed that the common standard deviation of EQ-5D-5L is 0.26, taking as a reference one of the articles by the principal investigator of this project, which evaluated the health-related quality of life through this questionnaire [20]. A follow-up loss rate of 20% has been estimated. 

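### The planned sensitivity imputation, built from baseline data and completers, cannot show what happens if dropouts fare differently, and in general does not avoid bias

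*Protocol article*

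**What the plan says.** Section 2.8 of the protocol article defines the intention-to-treat analysis: "This analysis will include all randomly assigned participants in their corresponding groups". For missing values, "Multiple imputations will be used to impute lost data". Effects are then estimated with a "repeated measures ANCOVA test, adjusted by age and baseline values". No assumption about why data are missing is named.

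One sentence covers sensitivity to missing data. It says that "the data imputation will be made from the baseline patient data and from those participants who completed the study", and gives the reason: "in order to avoid estimation biases". No other missing-data sensitivity analysis is described.

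Section 2.3 sets the scale of the problem: "A follow-up loss rate of 20% has been estimated". Table 2 schedules most secondary outcomes for both groups at baseline and months 3, 6, 9, 12 and 13. Falls are scheduled at baseline and months 6, 12 and 13. The cost-effectiveness row, to which section 2.7.1 ties the EQ-5D-5L, is scheduled at baseline and months 12 and 13.

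**The concern.** A sensitivity analysis for missing data is useful when it changes the assumption on which the main analysis rests. Multiple imputation as usually applied assumes missing at random: given the observed data, the women who are missing resemble those who are seen. Filling gaps from baseline data and completers makes the same kind of assumption with less information, because the interim values of women who later leave are not used.

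The setting makes a departure plausible. Participants know their group (section 2.1). One arm is asked to train three times a week for 12 months (section 2.6), while the other continues usual care. Loss may therefore differ between arms or be linked to outcome, and women lost from Tele-SSE may not keep the benefit seen in completers. If so, the main and sensitivity estimates could err in the same direction, and their agreement would be read as robustness.

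**Working it through.** **Inputs.** From section 2.3: difference 0.15, SD 0.26, two-sided alpha 0.05, power 0.80, loss 20%. The documents give no split of loss by arm, no dropout mechanism and no correlation between visits. Those are assumptions below.

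**1. The plan's own figure.** n per arm = 2 × [0.26 × (1.960 + 0.842) / 0.15]² = 47.16. Allowing for loss, 47.16 / 0.8 = 58.95, so 59 per arm and 118 in total. The stated size reproduces and is not in question. Of 59 women, 0.20 × 59 = 11.8, or about 12 per arm, would have imputed values.

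**2. Completer-based reading, with benefit lost.** Assume completers gain 0.15 over control, Tele-SSE women lost to follow-up gain nothing, loss is 20% in each arm, and imputation is done within arm.
- Intention-to-treat effect: 0.8 × 0.15 + 0.2 × 0 = 0.12.
- Completer-based imputation: 0.8 × 0.15 + 0.2 × 0.15 = 0.15.
- Control-referenced imputation: 0.8 × 0.15 + 0.2 × 0 = 0.12.

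The overstatement is 1/(1 − loss) − 1, which is 25% at 20% loss, 11% at 10% and 43% at 30%. These figures follow entirely from assuming zero benefit.

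**3. Outcome-related dropout.** This is a large-sample simulation of regression imputation within arm. It assumes a true effect of 0.15, SD 0.26, visit correlations of 0.6 to 0.7, and dropout odds that rise e-fold per SD of worse outcome. Here dropouts keep the treatment effect, unlike in step 2. The simulation also assumes that an interim value of the outcome itself exists. For the EQ-5D-5L, Table 2 appears to offer only related interim measures.

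| Dropout, Tele-SSE / control | Driven by | Baseline + interim | Baseline + completers | Baseline carried forward |
|---|---|---|---|---|
| 20% / 20% | final outcome, unobserved | 0.151 | 0.151 | 0.121 |
| 30% / 10% | interim outcome | 0.149 | 0.164 | 0.106 |
| 30% / 10% | final outcome, unobserved | 0.172 | 0.179 | 0.115 |

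The full-data estimates in the three rows were 0.151, 0.149 and 0.150. Equal loss with the same mechanism gives no bias under the completer-based reading. In the second row the sensitivity method adds a bias of 0.164 − 0.149 = 0.015 that an imputation using interim data does not have. In the third row both imputations are too high, by 0.022 and 0.029. With a true effect of zero and the third row's dropout, they gave 0.022 and 0.029.

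**4. Carry-forward reading.** Let control women change by c over the year, completers in Tele-SSE by c + 0.15, and let loss be dT and dC, unrelated to baseline. The estimate is (1 − dT)(c + 0.15) − (1 − dC)c = 0.15(1 − dT) + c(dC − dT).
- At 20% in each arm this is 0.12 whatever c is. That is correct if dropouts lose the benefit, and 0.03 too low if they keep it.
- At 30% versus 10% it is 0.105 − 0.20c, so control drift now enters.

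**The case against.** The strongest reply is that the sentence is ambiguous. It speaks of sensitivity analyses in the plural and may describe a baseline-based and a completer-based analysis. Carrying baseline forward does depart from missing at random, and in the scenario of step 2 it returns 0.12, the intention-to-treat effect. The plan could then expose the gap between 0.15 and 0.12. This stands: the criticism that the two analyses share one assumption applies only to the completer-based reading.

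Three stronger conclusions are tempting, and the documents do not support them.
- **That the trial will overstate its effect by 25%.** That figure assumes zero benefit in every Tele-SSE woman lost. It also treats loss to follow-up as if it were stopping training. The 20% in section 2.3 is loss to follow-up, and Table 2 schedules both groups for assessment. Women who stop training but still attend are observed, not imputed.
- **That the sensitivity analysis will agree with the main one whatever the truth.** In step 3 the two differ in one scenario, and under carry-forward they differ in all of them.
- **That the plan is at fault for being unable to test missing at random.** No analysis of the observed data can strictly test it, and the document does not claim to. The fair wording is that the planned analysis cannot probe departures from it.

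It can also be said that imputation details belong in an analysis plan that is not shown. That is true of the imputation model and its auxiliary variables. It does not cover this sentence, because the article itself fixes the source of the imputed values and the purpose, and the two do not match.

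**Conclusion.** The point holds in a limited form. On its natural reading, the sensitivity imputation assumes that dropouts do as well as completers with the same baseline. It shares the missing-at-random assumption implied by the main analysis (inferred from standard multiple imputation, since the article names none) and cannot show what follows if that assumption fails. On the carry-forward reading it replaces that assumption with a single fixed one, whose bias depends on the dropout split, on drift, and on whether dropouts keep the benefit. Neither reading supports the stated purpose in general.

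The size is illustrative: 0.15 against 0.12 under assumed zero benefit at 20% loss, or about 0.015 to 0.03 too high under an assumed 30% versus 10% split. With equal loss and the same mechanism in both arms it may be zero. The sample size is unaffected. The change is worth making because it is cheap and makes the robustness check informative.

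**What to change.** 1. In the main imputation, use all observed post-baseline data, including the scheduled interim visits and the data of women who stop training but still attend, and name the assumption.
2. Replace the sensitivity sentence with, for example: *Robustness to departures from missing at random will be assessed by (a) control-referenced multiple imputation, in which missing Tele-SSE outcomes are imputed from the usual-care arm, and (b) a tipping-point analysis, in which imputed Tele-SSE values are worsened in fixed steps until the conclusion changes.*
3. Change the stated purpose from "in order to avoid estimation biases" to *to assess robustness to departures from missing at random*.

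A simple scale for the tipping-point steps: if Tele-SSE dropouts are worse than imputed by 0.05 to 0.15, the estimate falls by 0.2 × 0.05 = 0.010 to 0.2 × 0.15 = 0.030 at 20% missing, and by 0.015 to 0.045 at 30%.

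The cost is a revised paragraph and some extra code, with no new data. The downside is that the sensitivity estimate may be less favourable than the main one.
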